### Selection of participants

For the assessment of the method’s effectiveness, a sample size of 22 individuals has been estimated (11 for the IG and 11 for the CG, with a power of 80% and a confidence of 95%, expecting a risk/prevalence difference of 63% post-intervention (48). The final size of 50 individuals has been established (25 for the IG and 25 for the GC) to minimize the effect of possible losses and the low study completion rates, especially in participants with significant negative symptoms. Participants who express a clear wish to participate voluntarily in the study will be assigned, through randomization in balanced blocks, to the IG or CG (Figure 1). Randomization will be conducted according to the results found in stool culture analysis (balancing the prevalence of dysbiosis in both groups). Concerning the established inclusion/exclusion criteria, these will be:

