### Limitations

Potential limitations lie in the sample size of subjects included during the recruitment phase, the possible loss or non-cooperation of participants, and the loss or non-cooperation of participants in the intervention phase (especially those subjects with a predominance of negative schizophrenia symptomatology). This fact can lead to a possible lack of representativeness of the target population. Thus, to reverse this situation, the recruitment of the target population will be increased (more than doubled).

Likewise, the lack of capacity to prescribe symbiotic formulas and placebo management by mental health nurses, according to the legislative context in which the study will be carried out, prevents us from knowing the accurate range that an intervention with a high symbiotic content could have on these patients. Nevertheless, it is essential to emphasize that the main objective of the intervention is to assess the efficacy of a strategy based on health education. This tool is very cost-effective and is available for nursing professionals. Furthermore, from our perspective, this intervention can significantly impact the lifestyle habits of these patients in a sphere that has been forgotten as part of the traditional treatments.

Finally, the available evidence on the object of study makes it difficult to contrast the results obtained in different contexts of application.

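### Marked negative symptoms, the only patient characteristic the plan ties to loss, are neither balanced at assignment nor listed for adjustment, although PANSS is measured at baseline

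*Protocol article*

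**What the plan says.** All references are to the protocol article.

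- **Size and loss.** Under Selection of participants, "a sample size of 22 individuals has been estimated (11 for the IG and 11 for the CG"), and this is then raised: "The final size of 50 individuals has been established (25 for the IG and 25 for the GC"). The stated reason is "to minimize the effect of possible losses and the low study completion rates, especially in participants with significant negative symptoms".
- **Loss again.** The Limitations section speaks of loss and non-cooperation in general, "especially those subjects with a predominance of negative schizophrenia symptomatology". Its answer is that "the recruitment of the target population will be increased (more than doubled").
- **Assignment.** Participants are allocated "through randomization in balanced blocks, to the IG or CG", and one balancing factor is named: "Randomization will be conducted according to the results found in stool culture analysis (balancing the prevalence of dysbiosis in both groups").
- **Baseline PANSS.** Study design has PANSS and PSP taken at the start, at 3 months and at 6 months. Block 1 of the Work plan collects PANSS in the same phase as the stool culture.
- **Analysis.** The Statistical analysis section names t-tests, chi-square or Fisher tests, repeated-measures ANOVA, and logistic regressions that adjust for the independent variables. Those variables are listed under the sociodemographic, therapeutic and clinical headings. PANSS is not among them; it appears only under Result variables.

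**The concern.** The plan identifies one kind of patient as especially likely to drop out and responds only with more recruits. More recruits keep the number of completers up. They do not make the completers in the two arms alike on the characteristic that predicts dropping out.

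That characteristic also bears on outcome, because negative symptoms are part of PANSS, one of the two clinical efficacy scales. With 25 per arm, chance alone can leave one arm with noticeably more of these patients. The analysis as written would take this up only for PANSS itself, through the repeated measures. For PSP, diet and the cardio-metabolic outcomes, nothing listed takes account of it.

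**Working it through.** **1. The plan's own figure.** The inputs are "with a power of 80% and a confidence of 95%, expecting a risk/prevalence difference of 63% post-intervention". Only the difference d = 0.63 is given, so the control rate p2 has to be varied from 0 to 0.37.

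- Two-sided formula per arm: n = [1.96·√(2·p̄·(1−p̄)) + 0.842·√(p1(1−p1) + p2(1−p2))]² / d², where p̄ is the mean of p1 and p2.
- Continuity correction: n′ = (n/4)·[1 + √(1 + 4/(n·d))]².
- At p2 = 0, p1 = 0.63: n = (1.288 + 0.406)²/0.397 = 7.2, and n′ = 10.2, so 11 per arm.
- At p2 = 0.185, p1 = 0.815: n = 8.6, and n′ = 11.6, so 12 per arm.

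Over the whole range the corrected formula gives 11 to 12 per arm, or 22 to 24 in total, so the stated 22 reproduces. Going from 22 to 50 implies room for 1 − 22/50 = 56% loss. The article states no dropout rate, so 56% is an inference.

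**2. Chance imbalance in negative symptoms.** Suppose K of the 50 have marked negative symptoms. The article gives no prevalence, so K is assumed at 10, 15, 20 and 25. If assignment to 25 v 25 ignores the symptom, the number in one arm is hypergeometric(50, K, 25).

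| Assumed K (prevalence) | SD of the difference, points | P(20 points or more) | P(28 points or more) |
|---|---|---|---|
| 10 (20%) | 11.4 | 0.074 | 0.011 |
| 15 (30%) | 13.1 | 0.217 | 0.062 |
| 20 (40%) | 14.0 | 0.148 | 0.042 |
| 25 (50%) | 14.3 | 0.258 | 0.089 |

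Twenty points is 5 patients out of 25. The third column does not rise steadily because, when K is even, the difference must be even, so the smallest qualifying gap is 6 patients. For K = 20 that is a 13 v 7 split. A 12 v 8 split or worse has probability 0.387.

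For a continuous score, the standard error of the standardized difference is √(2/25) = 0.283. Then P(|difference| > 0.3) = 29% and P(|difference| > 0.5) = 8%.

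**3. What such a split does.** Take 13 v 7, with assumed loss of 70% in patients with marked negative symptoms and 45% in the others.

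- Baseline shares: 13/25 = 52% and 7/25 = 28%, a gap of 24 points.
- Expected loss: 13(0.70) + 12(0.45) = 14.5 of 25 (58%), against 7(0.70) + 18(0.45) = 13.0 of 25 (52%).
- Completers: 3.9/(3.9 + 6.6) = 37%, against 2.1/(2.1 + 9.9) = 17.5%, a gap of about 20 points.

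The imbalance among completers is therefore mostly the imbalance already present at assignment. Loss narrows it slightly here, and the arms differ in expected loss by only 1.5 patients.

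Averaged over all allocations with K from 15 to 25, the gap in expected loss is:

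| Assumed loss, marked v other | Average gap, points |
|---|---|
| 70% v 30% | 4.3 to 4.6 |
| 50% v 20% | 3.2 to 3.5 |
| 60% v 40% | 2.1 to 2.3 |

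**4. What the planned analysis takes up.** Repeated-measures ANOVA brings in baseline PANSS when PANSS is the outcome. The t-tests and chi-square tests bring in nothing. The regressions adjust for a listed set without PANSS. A baseline covariate with correlation r to an outcome reduces the residual variance of the arm comparison by a factor of roughly 1 − r², and the planned unadjusted tests forgo this.

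**The case against.** The strongest reply is that nothing here is an error. Leaving one prognostic factor out of the balancing scheme is an ordinary choice in a trial of 50, and dysbiosis is a natural factor for an intervention aimed at the microbiota. Chance imbalance after randomization is random error, already covered by the 5% level and the 95% interval. This stands, and it rules out four stronger readings that a reader might infer:

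- **That the comparison is biased by not stratifying.** It is not. Bias would come from loss that differs by arm or depends on outcome, and stratifying at baseline does not prevent that.
- **That negative symptoms decide who completes.** Both sections single these patients out as especially at risk, and Limitations also speaks of loss in general. The text supports only that this is the one patient characteristic linked to loss.
- **That imbalance would drive unequal dropout.** Under the assumptions above the effect on loss is a few points.
- **That an adherence comparison is distorted.** Study design has the weekly adherence record kept by the intervention group, so no such comparison between arms is described.

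It can also be said that a final covariate list commonly belongs in an analysis plan, which is not shown. That carries some weight. But the article is not silent: it says which variables are used for adjustment and lists them, and the one characteristic it links to loss is absent.

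**Conclusion.** The point holds as a specific improvement to the analysis; it does not correct an invalid design. The plan names one patient characteristic linked to loss, answers with numbers alone, balances a different factor, and leaves the measured baseline score out of its adjustment set. An imbalance of 20 points or more has probability of about 7% to 26%. It would leave the randomized comparison valid, but it can distort the sample obtained and costs precision.

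The range rests on assumed prevalences of 20% to 50% and on assignment that is unrelated to negative symptoms. The loss figures rest on assumed rates that the article neither gives nor contradicts.

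**What to change.** State that the baseline PANSS negative subscale score is a prespecified covariate in the between-arm comparisons of PANSS, PSP, diet and cardio-metabolic outcomes. ANCOVA suits outcomes measured at baseline and 6 months, and a mixed model suits those measured more often; either would replace the unadjusted t-tests. Add the score to the independent variables for the logistic regressions. Because the article lists PANSS as categorized, say that the numerical subscale score is kept. The cost is a change of text and one more model term, with no new measurement.

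Optionally, if the allocation list is not yet made, add the score, split at a fixed cut, as a second binary balancing factor beside the stool result. That gives four strata averaging 50/4 = 12.5 patients, fewer in some if dysbiosis is uncommon, with some incomplete blocks. Replacing the stool factor would instead give up balance on a baseline stool measure. This step is a trade-off for the sponsor, and the covariate is worth having either way.

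The covariate makes the results more robust to loss related to baseline negative symptoms. It does not remove bias from loss that differs by arm or depends on outcome beyond what that score explains, and the text should not suggest that it does.

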**FIGURE 1 F1:**
[figure not shown]
Flow chart of the participants (CONSORT diagram).

#### Inclusion criteria

-Patients diagnosed on the spectrum of schizophrenia (without distinction by type), according to criteria DSM-5 and/or ICD-11.-Age between 18 and 65 years.-Absence of gastrointestinal comorbidity that contraindicates the use of prebiotics and/or probiotics (intolerance, explosive diarrhea, acute abdominal pain, etc.).-To show clinical stability for 6 months before the start of the study (absence of psychiatric hospitalization, maintenance of the level of functionality, and lack of social and occupational absenteeism).-To manifest agreement to participate in the study and to sign of informed consent (Supplementary Appendices I–III).

#### Exclusion criteria

-To suffer from somatic or neurocognitive situation that prevents participation and collaboration in the fulfillment of the protocol.-To follow standardized dietary planning not modulated by the population under study (catering, institutional or collective feeding, etc.).-Concomitant administration of antibiotherapy during the intervention phase.-Refusal to participate in the study.

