The study will begin with a group session for the presentation of the research project in the health center and/or psychiatric service consultation. During the development of the study, data will be collected on the psychopathological state [Positive and Negative Syndrome Scale (PANSS) (45) and Personal and Social Functioning Scale (PSP) (46) scales; Supplementary Tables 1, 2], and blood test (hemogram, lipid profile, etc.). Measures will be taken at the beginning (basal), at 3 and 6 months. The estimation of intestinal microbiota and the usual nutritional pattern will also be assessed at the beginning and 6 months, using a stool test and a validated Food Frequency Questionnaire (FFQ) (47), respectively. The use of the FFQ will allow us to know both the average intake of grams of fiber, fat, etc. and the frequency of consumption by food groups (with particular attention to fermented foods). However, the main reason for using this tool is that it will allow us to assess changes in dietary patterns over the medium term (39). To evaluate the degree of adherence, participants in the IG will fill a specific weekly record of the main dishes/food consumed with a high prebiotic and/or probiotic content will be measured by the weekly completion (during the 6 months of intervention) of a record that includes the main foods consumed with a high symbiotic value (fermented foods, whole grains, green leafy vegetables, fruit, etc.) (Supplementary Figure 1). This record will be completed by the patients themselves or, in cases of incapacity or lack of autonomy in preparing the dishes consumed by family members or the primary caregiver. At least, anthropometric parameters will also be analyzed monthly (BMI, blood pressure, heart rate, abdominal perimeter) (Supplementary Table 3).

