The second block includes the implementation of the 6-month individual nutrition education program (associated with 2 months of educational reinforcement, according to block 3). It will consist of eight sessions, the first four being biweekly, followed by 4 monthly, to which four sessions of educational reinforcement will be added to the 3 and 5 months of study. The minimum duration of each session has been established for 30 min. However, this length could be different, considering the characteristics of the participants. The control group will be made up of those participants who will receive standardized dietary advice (35). In this sense, the education content in the intervention group will be based on general principles of conventional dietary advice in an intensified manner (36), centered on the acquisition of specific knowledge about: (I) Underlying mental pathology, lifestyles and associated comorbidities; (II) Immediate principles: Carbohydrates, lipids, proteins, fiber, vitamins, and minerals; energy needs; consumption requirements; (III) Water requirements; (IV) Foodstuff; (V) Description and justification of prescribed prebiotic and probiotic diet; (VI) Culinary techniques: conservation of properties of the prebiotic and probiotic diet; (VII) Optimal distribution and interchange of foods with high prebiotic and probiotic content; (VIII) Feeding in particular situations.

In both the IG and the CG, visual support resources will be used during the development of the established sessions.

#### Block 3

Finally, to evaluate the effectiveness of the intervention, the modification in the nutritional, the cardio-metabolic, and the psychopathological area will be assessed. For doing this, researchers will carry out anthropometric determination, clinical evaluation, the performance of stool culture, and the study of the dietary pattern, as we commented above.

Likewise, in this block, an educational reinforcement (both in IG and CG) of what was treated in Block 2 will be offered, 3 and 5 months after the beginning of the block, every 15 days for the IG and monthly for the CG.

Once the intervention is concluded, the analysis of the collected data will be performed, culminating in the development of the scientific production and the writing of the research report.

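### Antibiotic use during the intervention phase is listed as an exclusion criterion, so as written it excludes participants who are already randomised

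*Protocol article*

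**What the plan says.** Under Exclusion criteria, the article lists: "Concomitant administration of antibiotherapy during the intervention phase".

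Under Selection of participants, those who agree to take part "will be assigned, through randomization in balanced blocks, to the IG or CG". The same paragraph adds that "Randomization will be conducted according to the results found in stool culture analysis", with the aim of balancing dysbiosis between the intervention group (IG) and the control group (CG).

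Under Work plan, Block 1 covers selection, recruitment and baseline assessment, and Block 2 is the "implementation of the 6-month individual nutrition education program".

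On contact with participants, Study design says that "participants in the IG will fill a specific weekly record of the main dishes/food consumed" and that "anthropometric parameters will also be analyzed monthly", the latter with no restriction to one arm. Block 3 sets reinforcement sessions "every 15 days for the IG and monthly for the CG".

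The Statistical analysis section does not say how a participant who meets the antibiotic criterion is handled.

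**The concern.** An exclusion criterion should be decidable before allocation. This one depends on something that can happen only afterwards. If it is applied, the groups compared at 6 months are no longer the groups that were randomised.

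That would be harmless only if antibiotic use were unrelated to outcome, or if removal selected the same kind of participant from both arms. The article's own text makes neither safe to assume. Its Background says that the microbiota influences the immune response, so a diet meant to change the microbiota might change infections and hence antibiotic use. Its Justification describes a population with excess deaths from infectious and respiratory disease, more smoking and resistance to physical health care, so antibiotic users may well have a different prognosis.

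At stake are all outcomes, not only the stool culture. An excluded participant's weight, blood pressure, blood tests and psychopathology scores would be lost as well. The balance on dysbiosis holds for the full randomised set and need not survive later removals.

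**Working it through.** **Step 1: timing.** Setting the sections side by side:

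- Allocation follows consent and uses a stool-culture result (Selection of participants). That culture belongs to Block 1.
- The 6-month programme is Block 2, after recruitment and baseline assessment.
- The Limitations section also separates a recruitment phase from an intervention phase.

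So the phase named in the criterion lies after randomisation. Reading it as antibiotic use at entry does not fit the words.

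**Step 2: the plan's own sample size.** Inputs from Selection of participants: power 80%, confidence 95%, difference d = 0.63, 1:1 allocation. The two component rates are not given, so the lower rate is varied from 0 to 0.37. Per arm,

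n = [1.96·√(2p̄(1−p̄)) + 0.842·√(p1(1−p1) + p2(1−p2))]² / d²,

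and with continuity correction n' = (n/4)·[1 + √(1 + 4/(n·d))]².

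Example with p2 = 0.05 and p1 = 0.68: n = 7.87 and n' = 10.8, that is 11 per arm. Across the rates tried, n' is 11 (lower rate 0-0.05 or 0.35-0.37) or 12 (0.10-0.30), a total of 22 to 24. The stated 22 is reproduced and does not depend on the antibiotic rule.

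**Step 3: loss of numbers.** The article gives no antibiotic rate; assume 10-30% over 6 months. If every user is removed, 25 × (1 − 0.10) = 22.5 to 25 × (1 − 0.30) = 17.5 per arm remain, above the stated 11. Overall, 50 against 22 tolerates 1 − 22/50 = 56% loss from all causes. Numbers are not the problem.

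**Step 4: bias, as an illustration.** Let a be the share using antibiotics (equal in both arms), d_arm the share of users detected and removed in an arm, and assume no treatment effect, with 50% of non-users and 20% of users improving. Then

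retained response = [(1−a)·0.50 + a·(1−d_arm)·0.20] / (1 − a·d_arm).

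In the IG with full detection this is 0.50. In the CG:

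| a | CG response, half detected | IG − CG | CG response, none detected | IG − CG |
|---|---|---|---|---|
| 0.10 | (0.45 + 0.01)/0.95 = 0.484 | 1.6 points | 0.47 | 3 points |
| 0.20 | (0.40 + 0.02)/0.90 = 0.467 | 3.3 points | 0.44 | 6 points |
| 0.30 | (0.35 + 0.03)/0.85 = 0.447 | 5.3 points | 0.41 | 9 points |

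With equal detection in this model the difference is 0. If detection were better in the CG, the same figures would appear with the opposite sign. On a continuous scale, with 100% against 50% detection, users doing 0.5 SD worse at 20% use gives (0.10 × 0.5)/0.90 = 0.056 SD. Users doing 1 SD worse at 30% use gives (0.15 × 1)/0.85 = 0.176 SD. Every rate in this step is assumed.

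The model leaves out one route. If the diet itself changes who needs antibiotics, the remaining non-users differ between arms even when detection is perfect. The documents give nothing from which to size that.

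**Step 5: is detection unequal?** If reinforcement is given in two months (3 and 5), sessions every 15 days make about 2 × 2 = 4 in the IG and monthly sessions make 2 in the CG, about two extra IG contacts. The IG-only weekly record lists foods, not medicines. Monthly anthropometry brings both arms in. Unequal detection is possible, but its size cannot be derived.

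**The case against.** The strongest reply is that the article never describes a removal step. How such participants are followed and analysed may be set out in a full protocol or analysis plan not shown here, and the participant flow chart is not reproduced. That is fair, and the absence of a stated analysis population is not itself counted against the article. The criterion is stated, however. Its ordinary meaning is exclusion, and nothing in the text shown keeps these participants in.

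A reader might go further and infer that antibiotic use is more likely to be noticed in the IG, so that the exclusion favours the diet. The documents do not support that. They do not say how antibiotic use is ascertained in either arm, the weekly record concerns food, and both arms have monthly measurements. The contrast of 100% against 50% detection, and the 0.06-0.18 SD that follows, are illustrations only.

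A reader might also infer a damaging loss of power, since the detectable difference for a t-test rises from 0.81 SD at 25 per arm to 0.91 SD at 20. That is not the basis on which the trial was sized. On its own basis, 17.5 per arm still exceeds 11, and the increase to 25 was made to absorb losses.

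Finally, the line serves a purpose. It is the only antibiotic restriction in the eligibility lists, the Background names antibiotics as a determinant of the microbiota, and allocation depends on the baseline stool culture. Simply deleting it would leave that stratifying result unprotected. This objection stands, and it shapes the fix.

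**Conclusion.** The point holds in a limited form. Eligibility is made to depend on an event after randomisation, which the text establishes directly. That the participants are then dropped is the natural reading of an exclusion criterion but is not spelled out.

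The consequence is a possible selection bias of unknown size and sign on all outcomes, with possible loss of the dysbiosis balance. The illustrated 1.6 to 5.3 points (up to 9 if no CG use is detected) rest wholly on assumed use, outcome and detection rates. The figure falls to zero with equal detection and use unaffected by the diet. It is modest beside the 63-point difference used for sizing. Neither better detection in the IG nor inadequate power is shown.

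This should be fixed, because the remedy is cheap and data not collected after an exclusion cannot be recovered. It is not a fatal defect.

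**What to change.** 1. Reword the criterion so that eligibility depends only on facts known before randomisation. Do not merely delete it, since the baseline stool culture determines allocation. The clinical content of the entry rule is for the investigators to set.
2. Record antibiotic courses in both arms with the same question at the same visits. The monthly anthropometry visits already offer a common occasion.
3. State that all randomised participants are followed and analysed in their allocated group, whatever antibiotic use occurs later. This keeps 25 per arm and needs no new sample size.
4. For the stool-culture outcomes, add a sensitivity analysis that accounts for antibiotic use before the 6-month sample. Label it as a non-randomised comparison: stool is taken only at baseline and 6 months, so setting aside a sample removes that participant's whole follow-up result.

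The cost is a short amendment, one item on the visit form and one extra analysis. The downside is some dilution of the microbiota effect in the main analysis, which the sensitivity analysis helps to show. The change should be made before anyone is removed under the present wording.
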